## Methods

### Design

We will conduct a parallel eight-armed randomized controlled pilot study (see Fig. 1 for the study flow and supplemental materials for the spirit checklist of the trial). The study will be conducted at the Department of Clinical Psychology and Psychotherapy of the Friedrich-Alexander-Universität Erlangen-Nürnberg. In the eAAMT and swipe control groups, participants will receive four sessions à 20–30 min of training on four consecutive days, while the inactive control group will not receive any training. Participants will be randomly assigned to one of the eight study groups with a 1:1 allocation. A postdoctoral researcher not otherwise involved in the study will generate a randomization list using random numbers in Microsoft Excel. A block randomization will be performed with a block size of eight. The study is registered in the German Clinical Trials Register (Deutsches Register Klinischer Studien; DRKS00023007).

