### Participants

Inclusion criteria for participation in the pilot study will be the following: (1) heightened levels of perceived stress as indicated by a score of 19 or above on the Perceived Stress Scale-10 (PSS-10; German version: [66]), (2) at least 18 years of age, and (3) ability and willingness to provide informed consent. Following procedures suggested by Heber and colleagues [67], the PSS cut-off score is set at one standard deviation above the PSS mean score in the validation study of the German version of the PSS-10 [66]. Exclusion criteria will be as follows: (1) the presence of a severe psychological condition (i.e., psychosis; based on self-report), (2) physical conditions impairing the expression of emotion (e.g., facial paralysis), (3) heavy smoking (i.e., more than 10 cigarettes/day due to possible confounding influences on cortisol measures), and (4) suicidal ideation. We expect a medium to large effect size based on previous smartphone-based AAMT studies (e.g., [52, 53]). Therefore, we will include *n* = 10 participants per study group (i.e., *N* = 80 in total) as suggested by Bell and colleagues [68] for pilot studies with expected medium to large effect sizes. To complete the intervention per protocol, participants should attend at least three of the four training sessions. To ensure even distribution of subsample sizes across study conditions, we will change randomization block size in case of treatment dropouts. Number of and reasons for dropping out will be recorded and reported for each condition.

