#### Control interventions

*Swipe control condition*: In the swipe control condition, participants will use the same app as in the experimental conditions. Here, the app will also provide participants with written instructions but without showing video clips. To approach and avoid the stimuli, participants will be asked to swipe stress-enhancing beliefs away from themselves and stress-reducing beliefs towards themselves on the smartphone screen. After swiping, the app will provide a respective zoom feedback and present a thumbs-up picture (see description of the experimental conditions). In the swipe control condition, the app will not be controlled by an experimenter. The participants will still be observed with an external video camera during the training to keep the conditions between experimental and control intervention equal.*Inactive control condition*: Participants randomized to the inactive control condition will not be invited to the lab and receive any training. They will receive links to the study questionnaires via email and fill them out by themselves.

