### Statistical analysis plan

Before conducting the analyses, we will test the preconditions and in case of violations use alternative methods. The level of significance will be set to *α* = 0.05. We will report *p*-values for all analyses.

Feasibility outcomes will be analyzed with descriptive statistics and independent *t*-tests to compare the results of the eAAMT conditions with the swipe control condition. To gain insight into the differences in clinical outcome measures between study conditions, we will compute pre-post effect sizes. In addition, we will conduct exploratory analyses using two-way mixed analyses of variance (ANOVAs) with treatment as between-subjects factor and time as within-subjects factor. Because omnibus tests fail to detect differences between single conditions if the majority of conditions do not differ, we plan to run pairwise comparisons comparing the single eAAMT conditions with the inactive control condition and the swipe control condition. In order to prevent alpha-error accumulation, we will first compare the eAAMT conditions to the inactive control condition. Only if the interaction effect in this comparison will be significant, we will also compare the eAAMT conditions to the swipe control condition. Moreover, as this is a pilot trial and we aim to evaluate if the training is effective in itself, we will conduct per protocol analyses. We will also run intention-to-treat analyses to determine the robustness of the results when considering missing data. All analyses will be conducted in R [91] and SPSS.

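### Per-protocol analysis leads the efficacy assessment, but its session rule can remove only trained participants, so the gatekeeping comparison with inactive controls is no longer protected by randomisation

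*Protocol article*

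**What the plan says.** - **Analysis sets** (Statistical analysis plan). The per-protocol choice comes with its reason: "as this is a pilot trial and we aim to evaluate if the training is effective in itself, we will conduct per protocol analyses". Intention-to-treat follows with a different purpose: "We will also run intention-to-treat analyses to determine the robustness of the results when considering missing data".
- **Per-protocol rule** (Participants). "To complete the intervention per protocol, participants should attend at least three of the four training sessions". No other per-protocol criterion is given.
- **Who has sessions** (Design). In the six eAAMT arms and the swipe arm, "participants will receive four sessions à 20–30 min of training on four consecutive days, while the inactive control group will not receive any training". Under Control interventions, members of the inactive arm "will not be invited to the lab and receive any training"; they complete emailed questionnaires on their own.
- **Order of testing** (Statistical analysis plan). "we will first compare the eAAMT conditions to the inactive control condition". Then: "Only if the interaction effect in this comparison will be significant, we will also compare the eAAMT conditions to the swipe control condition".
- **Data after discontinuation** (Procedures). People who stop the intervention are still asked for their assessments. The same section says that neither participants nor experimenters are blinded.

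**The concern.** A per-protocol set is formed after randomisation, and here it is formed in one direction only. A trained participant who misses two or more sessions leaves the set. A comparable person allocated to the inactive arm has nothing to attend and stays in.

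Attendance may well be related to outcome. Allocation is known, the trained arms must come to the lab on four consecutive days, and eAAMT participants act out emotions while an investigator watches. The Discussion accepts that the investigator's presence may affect performance, particularly in socially anxious people.

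Two things are at stake. The inactive comparison is the one meant to show whether the eAAMT helps at all, and a significant result in it opens the swipe comparison. In addition, preliminary effect sizes ahead of a large RCT are a stated aim (Purpose of the study), and an estimate that mixes the training effect with the difference between adherent and non-adherent people is a poor basis for that trial.

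**Working it through.** **Plan's own figure.** Eight arms of 10 give 8 × 10 = 80, as stated. The protocol gives no expected exclusion rate and no power, so the size of the problem can only be illustrated.

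**Can the rule exclude anyone?**

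| Arm | Sessions offered | Can fail the three-of-four rule? |
|---|---|---|
| Six eAAMT arms | 4 | Yes |
| Swipe control | 4 | Yes |
| Inactive control | 0 | No |

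The asymmetry is structural and rests on no assumption. It concerns the inactive comparison. In the swipe comparison both sides face the same rule.

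**Illustration: inputs, all assumed.** The training has no true effect. The share q of a trained arm with the lowest adherence is excluded. The correlation between adherence and improvement is ρ, under a normal model. The control arm is intact.

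**Formula.** With z the q-quantile of the standard normal and φ its density,

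bias (in SD of change) = ρ × φ(z) / (1 − q).

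- q = 20%: φ(z) / (1 − q) = 0.280 / 0.80 = 0.350. Times 0.3 gives 0.105; times 0.5 gives 0.175.
- q = 50%: 0.399 / 0.50 = 0.798. Times 0.3 gives 0.239; times 0.5 gives 0.399.

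A simulation (40,000 runs per setting, t-test on change, two-sided α = 0.05, 10 completers against 10 controls) agreed with the formula. It also gave the rate of false significance in the training's favour, which is nominally 2.5%.

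| Excluded, q | Bias, ρ = 0.3 | Bias, ρ = 0.5 | False significance favouring training (ρ = 0.3 to 0.5) |
|---|---|---|---|
| 10% | 0.06 SD | 0.10 SD | 3.2% to 3.9% |
| 20% | 0.11 SD | 0.17 SD | 4.2% to 5.7% |
| 30% | 0.15 SD | 0.25 SD | 5.2% to 7.6% |
| 50% | 0.24 SD | 0.40 SD | 7.4% to 14.0% |

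**Sensitivity to direction.** With ρ = 0 the bias is zero at every q. With ρ = −0.3 it runs from −0.06 SD (q = 10%) to −0.24 SD (q = 50%), against the training.

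**Scale.** The protocol expects a medium to large effect without giving a number. If medium is read as d = 0.5, the bias at 20% excluded is 0.105 / 0.5 = 21% to 0.175 / 0.5 = 35% of it.

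**After the change.** With everyone analysed as allocated and outcomes complete, this exclusion bias is zero and the 2.5% is restored. Missing outcomes could still cause bias.

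**The case against.** The best defence is that this is a pilot. The ANOVAs are labelled exploratory, the Discussion calls the sample very small and leaves efficacy to a bigger study, and intention-to-treat is already planned. That lowers the severity. It does not settle which result counts, or which one opens the gate, if the two analyses disagree.

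Several stronger readings are tempting, and the documents do not support them:

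- **Per-protocol is declared primary.** It is not; neither analysis is ranked in those words. Its leading place follows from the order and from the reason attached to it. Nor does the protocol say which set operates the gate or supplies effect sizes for the RCT.
- **The bias certainly favours the training.** Nothing in the protocol says who will miss sessions. Scheduling or technical trouble could cause absence unrelated to outcome.
- **The whole gap between the per-protocol and intention-to-treat estimates is bias.** Suppose training works by 0.5 SD, non-completers gain nothing and there is no selection. With 25% excluded, the two estimates differ by 0.25 × 0.5 = 0.125 SD, all of it dilution. The illustration above avoids this by assuming no true effect.
- **Half of each trained arm will be lost.** The 50% under Feasibility of the intervention is a pass mark for completing as instructed, and it is not equated with the three-session rule. It marks an extreme case.
- **Every inactive control is retained.** The session rule removes none, but missing questionnaires still could.
- **The swipe comparison has the same one-sidedness.** It does not. It is affected only if completion differs between eAAMT and swipe, and through the gate.

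**Conclusion.** The point stands for the eAAMT versus inactive control comparison. The only stated per-protocol rule acts on one side of it, so the analysis given for judging effectiveness is not a randomised comparison. That follows from the text alone.

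The direction and size do not. A bias towards the training is the plausible direction. Under the assumed correlations of 0.3 to 0.5 and no true effect, it would be about 0.11 to 0.17 SD with 20% excluded and 0.24 to 0.40 SD with 50% excluded. The aim of learning whether the training works in itself does not rescue the choice: completers compared with an unselected control arm do not isolate the effect of training. The change should be made, but this is an exploratory pilot with intention-to-treat already planned, so the flaw does not undermine the trial as a whole.

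**What to change.** In the Statistical analysis plan:

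1. Make intention-to-treat the leading efficacy analysis: all randomised participants in their allocated arm, using the outcomes already sought from those who discontinue.
2. State that the gate to the swipe comparison, and the effect sizes carried to the RCT, come from this analysis.
3. Keep the per-protocol analysis as supplementary and label it a non-randomised comparison.

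**Cost.** A few sentences; no new data and no design change. The intention-to-treat estimate may be smaller because non-attendance dilutes it, and missing outcomes still need handling.

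**Optional.** A mixed model using all available PSS-10 values is one way to handle missing data. It would replace the planned ANOVA, so it is more than a reordering. If the screening score is included, note that it is truncated by the entry criterion of 19 or above. The core change does not depend on it.

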## Discussion

In this pilot study, we will evaluate the feasibility and explore the efficacy of a novel, emotion-based AAMT targeting stress-related beliefs in individuals with elevated perceived stress. Due to their important role in the emergence of perceived stress [20], stress-related beliefs are a promising starting point for interventions against stress. To our knowledge, this is the first study that employs an AAMT with stress-related beliefs as stimuli, thus targeting a construct directly implicated in the process of stress generation. Prior AAMT studies in the stress context that used emotional pictures as stimulus material mostly failed to find effects on stress measures [51, 54]. This demonstrates the need for a new way of designing AAMT interventions against stress, which our study addresses. Another novelty of our intervention is the use of emotions as approach/avoidance responses within an AAMT. Based on assumptions of the inferential account [35], we hypothesize that displaying highly valenced emotional responses within an AAMT will enhance the effects of currently performed AAMTs and be more effective in modifying approach-avoidance biases as well as reducing the particular psychopathology associated with such biases. In addition to their strong valence, the specific appraisals and behavioral tendencies associated with emotions [59] might be transferred to AAMT stimuli, thereby changing their evaluation in a more complex way. Therefore, in our study, participants will display emotional responses to push stress-related beliefs away from themselves and pull stress-reducing beliefs towards themselves. In order to provide an accessible and easy-to-disseminate training, we developed the eAAMT as app-based intervention. Since this is a completely new intervention, we decided to conduct a pilot study in preparation for a larger RCT. With the help of the feasibility evaluation, we will be able to gain insights into how the eAAMT can be implemented and is received by users. Moreover, we will be able to use the information on the feasibility of our study design to make further adaptations before the start of the RCT. By exploring the efficacy of the eAAMT, we will gain preliminary insights into its effects on clinical outcomes and, hence, therapeutic potential. We hypothesize that the eAAMT will be more effective in reducing perceived stress as well as the extent of agreement with dysfunctional beliefs and symptoms of depression than a swipe-based AAMT. In addition to exploring this hypothesis, we will explore whether the display of the emotions anxiety, anger, sadness, or disgust will be particularly effective and whether a bias towards approach responses within the eAAMT increases its efficacy. When we developed the protocol, we decided to use an inactive control condition as one of the comparators. This allows us to answer the question whether the eAAMT is helpful at all. As second comparator, we chose to use the swipe-based AAMT which is currently the most common AAMT variant on the smartphone [39–41, 52, 53]. The comparison with a swipe-based AAMT allows us to investigate whether the use of emotions in the AAMT provides additional benefit.

The current study has several limitations. First, we will use standardized stress-related beliefs that may not be relevant for every participant. However, we aim to develop an app that can be disseminated on a large scale and used by everyone and thus decided to standardize the material. Second, the eAAMT will be performed as a Wizard-of-Oz paradigm [92] in which the investigator assesses the emotional response as long as the algorithms are not able to do this (however, in contrast to a real Wizard-of-Oz paradigm, participants are informed that the investigator assesses the emotional response). The presence of an investigator, however, might have an impact on participants’ performance [93], especially if they are socially anxious, and therefore influence the efficacy of the app in reducing perceived stress. Thus, future studies should compare the efficacy of an investigator-based eAAMT with the automated version of the intervention. Third, our target sample size is very small. It is sufficient, however, to test the feasibility of the intervention and study design and explore its therapeutic potential. If the results of the intended study are promising, future studies should investigate its efficacy in a bigger sample. Fourth, we will not be able to draw conclusions about the long-term efficacy of the intervention. Thus, in case of evidence for short-term effects, future studies should include long-term follow-up assessments. Fifth, the compensation for study participation is not equal over the course of the study. Psychology students receive course credit at all times. Non-psychology students, on the other hand, did not receive compensation at the beginning of the study, but it was introduced during the course of the study. The presence of a compensation might reduce intrinsic motivation to participate in the intervention and thus affect the outcomes. However, we believe that course credit or a compensation of 20 € is not enough to be the only source of motivation to participate in such a study. Nevertheless, future studies should keep compensation equal. Finally, recruitment of the pilot trial already had started by the time this study protocol was written. This is not in line with good scientific practice which requires the publishing of study protocols before the start of the trial to increase transparency. However, to ensure transparency, this pilot study has been preregistered. We decided to additionally publish the study protocol because it allows us to describe the complex design and novel intervention in more detail.

All these limitations aside, if shown to be effective, the eAAMT has great potential to improve healthcare as it is an easy-to-deliver and engaging intervention. Moreover, approach-avoidance biases are implicated in many mental disorders [33]. Hence, increasing the efficacy of currently employed interventions might improve treatment in various domains of psychopathology. In addition, if, as endeavored in our study, the emotion recognition is automated with the help of machine learning methods and implemented in future interventions, such new, innovative approaches open up many possibilities to further reduce the burden on the healthcare system — important assets in order to address “the health epidemic of the twenty-first century” [1].

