The experimenters will explain the aim of the training and its implementation. In addition, the app will provide participants with short written instructions for the training which will be complemented with short video clips. Each training session will consist of 60 trials where the stimuli are presented in random order. With the exception of one condition (see below), the approach-avoidance response ratio will be 50:50. Upon presentation of a stimulus, participants will decide whether they should pull the respective belief towards themselves or push it away (i.e., whether it is stress enhancing or stress reducing). Participants will draw stress-reducing beliefs towards themselves by displaying one of twelve positive emotions. The training sessions will be divided into three blocks (20 trials each) with participants being instructed to change the emotional response after each block. The emotions will always be displayed in the same order (day 1: joy, relaxation, and love; day 2: excitement, tranquility, and gratitude; day 3: happiness, resolve, and content; day 4: courage, confidence, and pride). Stress-enhancing beliefs will be pushed away by displaying different negative emotions, namely anxiety, anger, disgust, and sadness. The instructive video clips will show an actor who carries out the display of each emotion. The video clips will address the following four components: (1) facial expression of the emotion, (2) a verbal statement consistent with the emotion, (3) the intonation of the verbal statement, and (4) a body gesture consistent with the emotion. When the correct emotion is displayed, the stimuli will either zoom in (approach) or out (avoidance), and a thumbs-up picture will be presented on the smartphone screen to systematically reinforce possible effects of the training. When the stimulus is not processed correctly, the sentence “Unfortunately, this was the wrong emotion” will appear on the screen. Figure 2 shows an exemplary trial flow. In all eAAMT conditions, an investigator will observe participants’ emotion display through a live stream of a video camera from behind a partition wall and remote control the app with a tablet. Smartphone and tablet are connected using Google’s Nearby Application Programming Interface (https://developers.google.com/nearby/), which automatically establishes either a Bluetooth or a Wi-Fi connection between the two devices.

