The six variations of the eAAMT are described in the following:*eAAMT anxiety*: In the eAAMT-anxiety condition, participants will be asked to push stress-enhancing beliefs away from themselves by displaying anxiety. Anxiety conveys the information that a stimulus is dangerous and cues avoidance tendencies [57, 70]. It might thus be helpful in increasing the avoidance motivation towards stress-enhancing beliefs. As instructed by the actor shown in the introductory video, participants are asked to express anxiety by a fearful facial expression and heavy breathing, by withdrawing the body, and saying “It is dangerous to think like that, I will protect myself from that!”.*eAAMT anger*: In the eAAMT-anger condition, participants will be asked to push stress-enhancing beliefs away from themselves by displaying anger. Anger is activated when someone or something is hindering a person to attain a personally relevant goal and when apologetic circumstances are not seen [57]. While anxiety cues avoidance tendencies, anger facilitates fighting for one’s goals [57]. Participants are instructed to display anger by an angry facial expression, a threatening clench of the fist, hitting the table, and saying “Such a stupid belief, I will not listen to its advice!”.*eAAMT disgust*: In the eAAMT-disgust condition, participants will be asked to push stress-enhancing beliefs away from themselves by displaying disgust. The evolutionary function of disgust was to detect contaminated/poisonous food or disease threat [71]. Therefore, it triggers strong aversion and is associated with avoidance tendencies [58, 70]. Disgust will be expressed by a disgusted facial expression, turning away one’s head, and saying “Ugh, this is disgusting, I will stay away from that!”.*eAAMT sadness*: In the eAAMT-sadness condition, participants will be asked to push stress-enhancing beliefs away from themselves by displaying sadness. Sadness provides the information that current goals are not attainable and cues a letting go of these goals, which eventually facilitates committing to other (more attainable) goals [57]. When used within the eAAMT, sadness might help participants to regret that they have developed dysfunctional beliefs and let go of them. Participants are instructed to display sadness by a sad facial expression and deep breath, tilting the head forward, and saying “I will let go of this belief!”.

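### The eAAMT-versus-swipe contrast estimates the effect of the whole eAAMT package, so a benefit cannot be assigned to the use of emotions alone

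*Protocol article*

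**What the plan says.** The Discussion presents the swipe-based training as the second comparator and gives its purpose: "The comparison with a swipe-based AAMT allows us to investigate whether the use of emotions in the AAMT provides additional benefit". The Background supplies the mechanism: emotional responses should transfer stronger positive or negative valence to the beliefs than finger or wrist movements do.

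Under Experimental interventions, each emotion display is taught through four components, one of which is "a verbal statement consistent with the emotion". For avoidance trials the script is fixed by emotion. For anger it is "Such a stupid belief, I will not listen to its advice"; for sadness it is "I will let go of this belief". On teaching, the section says: "The instructive video clips will show an actor who carries out the display of each emotion". The investigator follows the display "through a live stream of a video camera from behind a partition wall and remote control the app with a tablet". Performance measures adds that this investigator scores face, voice and body after every display. The Discussion confirms that participants are told of the assessment.

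Under Control interventions, the swipe arm uses the same app with the same zoom and thumbs-up feedback. It differs as follows: "Here, the app will also provide participants with written instructions but without showing video clips". No experimenter controls the app. On matching, the section says: "The participants will still be observed with an external video camera during the training to keep the conditions between experimental and control intervention equal".

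**The concern.** The Discussion reads a difference between eAAMT and swipe as information about emotions, but the arms differ in several things at once. Two of the additional elements are credible rival explanations on the protocol's own terms.

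First, the Background says that many stress trainings work by invalidating stress-related beliefs. Repeatedly rejecting a belief aloud resembles that route and could act without any emotional valence. Second, perceived stress and dysfunctional beliefs are self-reported, and Procedures states that neither participants nor experimenters are blinded. Knowing that every response is judged live could therefore affect the answers directly.

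The same problem reaches the exploratory comparison of anxiety, anger, sadness and disgust, because each emotion has its own sentence.

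The pilot is meant to prepare a larger RCT and an automated app. If a package effect is reported as an effect of emotion, the next trial may build on, and match for, the wrong component.

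**Working it through.** The plan states no figure on this point, so the check is a comparison of the arms by component, followed by a count of exposure.

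**Components by arm** (Experimental interventions, Control interventions, Performance measures, Discussion)

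| Component | eAAMT (all six variants) | Swipe control |
|---|---|---|
| App, belief statements as stimuli, written instructions | yes | yes |
| Zoom and thumbs-up feedback | yes | yes |
| Filming by external camera | yes | yes |
| Emotion display in face and body | yes | no |
| Scripted spoken statement | yes | none described |
| Actor videos | yes | no |
| Investigator judges the response live and operates the app | yes, known to participants | no experimenter control of the app |

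The last four rows change together. The inactive control has none of these components, and every eAAMT variant has all of them, so no pair of arms separates emotion from the spoken statement, the videos or the judging.

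**Exposure to the belief-rejecting sentence.** Inputs: 60 trials per session; four sessions; avoidance share 1/2 in all eAAMT conditions but one, and 1/5 in the 1:4 condition (one dysfunctional belief to four functional ones on average). Assumption: one sentence per avoidance trial.

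Formula: trials per session × avoidance share × sessions.

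- Five 1:1 conditions: 60 × 1/2 × 4 = 120.
- 1:4 condition: 60 × 1/5 × 4 = 48.
- At the per-protocol minimum of three sessions: 60 × 1/2 × 3 = 90 and 60 × 1/5 × 3 = 36.
- Swipe control: none described.

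**Exposure to live judging.** Each eAAMT trial, approach or avoidance, needs a display: 60 × 4 = 240 judged displays at full attendance. Swipe has no display to judge.

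**Content of the sentences.** All four avoidance scripts turn the participant against the belief, but in different terms: as dangerous (anxiety), as stupid and not to be obeyed (anger), as repulsive (disgust), or as something to release (sadness). The sadness script names no emotion and could be spoken while swiping. In the single-emotion arms, emotion and sentence are therefore fully confounded.

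**What the limitations cover.** The Discussion accepts that an investigator's presence may influence efficacy, especially in socially anxious participants, and recommends a later comparison with an automated eAAMT. It does not apply this to the swipe contrast and mentions neither the statements nor the videos.

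**The case against.** The strongest reply is that speech belongs to the protocol's definition of displaying an emotion. The Background builds on facial, gestural and verbal expression together, and the videos merely teach that display. On this reading the use of emotions means the full multimodal response, and swipe, described as the most common smartphone version, is a fair standard comparator. Much of this stands: the package is a legitimate intervention, and package versus standard is a valid contrast. It does not cover live judging and app control, which are not part of an emotion. Nor does it remove the cognitive content of the sentences, so the valence explanation remains untested by this contrast.

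Several stronger readings are tempting but not supported.

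- A reader might infer that the protocol claims to isolate emotion. It says only that the comparison allows the question to be investigated.
- A reader might take the camera sentence under Control interventions as a claim that the arms are equal in every respect. The same paragraph discloses the missing videos and the absence of experimenter control, so the sentence most naturally concerns being observed.
- A reader might want an inflated false-positive rate. The documents give no basis for the size of a non-emotion shift, and live judging could also reduce benefit in socially anxious participants. The swipe comparison is also tested only if the comparison with the inactive control is significant. No error rate can be defended.
- A reader might propose crediting emotion only where benefit tracks felt intensity. The Background expects an effect even without consciously felt emotion, and felt intensity is a non-randomised self-rating made after baseline.

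**Conclusion.** The concern holds as a fault of interpretation. Allocation, outcomes and analyses are not at fault here. A difference between eAAMT and swipe estimates the added effect of the whole package: multimodal display including the spoken statement, video modelling and investigator-judged feedback. It cannot be assigned to emotional valence alone, and differences between the four emotion arms cannot be separated from the wording of their sentences.

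The contrast in spoken rejection is large, at the 120 and 48 repetitions counted above. Those counts assume full attendance and one sentence per avoidance trial. The resulting bias in the outcomes cannot be sized from the documents, and its direction is open. The exploratory pilot status limits the immediate harm, but the sentence in the Discussion governs what the pilot may be said to have shown.

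**What to change.** - **Discussion, choice of comparators:** state that eAAMT versus swipe estimates the added effect of the whole eAAMT package over the standard swipe version, name its elements, and say that the effect cannot be assigned to emotional valence alone.
- **Control interventions:** limit the equality statement to observation by camera.
- **Discussion, limitations:** extend the investigator limitation to the swipe contrast, with bias possible in either direction. Add that the statements and videos also differ, and that differences between emotion arms are confounded with statement wording.
- **Optional analysis:** any regression of outcomes on felt intensity or expression ratings should be labelled exploratory and supportive, and should not serve as a rule for attribution.

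The cost is a few sentences and a narrower headline claim. No arm, procedure or data collection changes, so this can be done while recruitment is under way. Separating or matching the components is a choice for the later trial.
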